## Abstract

**Background:**

Hispanics, particularly men of Mexican origin, are more likely to engage in heavy drinking and experience alcohol-related problems, but less likely to obtain treatment for alcohol problems than non-Hispanic men. Our previous research indicates that heavy-drinking Hispanics who received a brief motivational intervention (BMI) were significantly more likely than Hispanics receiving standard care to reduce subsequent alcohol use. Among Hispanics who drink heavily the BMI effectively reduced alcohol use but did not impact alcohol-related problems or treatment utilization. We hypothesized that an adapted BMI that integrates cultural values and addresses acculturative stress among Hispanics would be more effective.

**Methods/Design:**

We describe here the protocol for the design and implementation of a randomized (approximately 300 patients per condition) controlled trial evaluating the comparative effectiveness of a culturally adapted (CA) BMI in contrast to a non-adapted BMI (NA-BMI) in a community hospital setting among men of Mexican origin. Study participants will include men who were hospitalized due to an alcohol related injury or screened positive for heavy drinking. By accounting for risk and protective factors of heavy drinking among Hispanics, we hypothesize that CA-BMI will significantly decrease alcohol use and alcohol problems, and increase help-seeking and treatment utilization.

**Discussion:**

This is likely the first study to directly address alcohol related health disparities among non-treatment seeking men of Mexican origin by comparing the benefits of a CA-BMI to a NA-BMI. This study stands to not only inform interventions used in medical settings to reduce alcohol-related health disparities, but may also help reduce the public health burden of heavy alcohol use in the United States.

**Trial registration:**

Trial registration clinicaltrials.gov identifier NCT02429401; Registration date: April 28, 2015.

## Background

### Drinking among Hispanics

Research indicates that heavy drinking and alcohol problems are highest among Hispanic men compared to men of other racial/ethnic groups in the United States [1]. Compared to non-Hispanics, Hispanics have higher rates of self-reported driving while intoxicated and arrests for driving under the influence of alcohol [2]. Hispanics are more likely than non-Hispanics to report workplace, legal, social and alcohol use related health problems [3–5]. Hispanics of Mexican origin have among the highest rates of heavy drinking, driving under the influence of alcohol, arrests for driving while intoxicated, alcohol abuse, and dependence [6–8]. Among Hispanics, men are more likely to drink and drink more heavily compared to women [9, 10], and men of Mexican origin are particularly vulnerable to alcohol problems [11, 12]. Despite the increased need for treatment of alcohol problems among Hispanics in the U.S., Hispanics are less likely than non-Hispanic whites to receive specialty treatment or multiple episodes of care [9, 13–15]. Explanations for the unmet need for alcohol-related treatment in the Hispanic population include factors such as immigration experiences, racial/ethnic discrimination, insufficient availability of bilingual clinicians, low socioeconomic status, and lack of or insufficient health insurance coverage [9]. Given the prevalence of alcohol problems among men of Mexican origin, there is a strong need for evidence based interventions that are culturally and linguistically responsive.

### Brief motivational intervention among Hispanics

Brief motivational intervention (BMI) is based on motivational interviewing (MI), which is a person centered, collaborative conversation style aimed at strengthening a person’s motivation and commitment to change by addressing ambivalence about change [16]. BMI following admission for treatment of an alcohol related injury is a conversation lasting about 25 min during which the clinician adheres to MI principles and the use of core clinical tasks associated with brief interventions [17–19]. In the first study sufficiently powered to evaluate ethnic differences in response to BMI targeting heavy drinking and its associated problems, we found that BMI was more effective than standard care with heavy-drinking Hispanics (82 % Mexican or Mexican American; 89 % male) admitted for medical treatment of an alcohol-related injury and/or whom recently engaged in heavy drinking [20]. Despite more severe alcohol problems and limited treatment utilization at baseline, Hispanic participants significantly benefited from BMI in terms of alcohol use compared to non-Hispanic participants [20]. However, BMI did not influence alcohol problems or treatment utilization [20].

We hypothesized that BMI did not significantly affect alcohol problems and treatment utilization because it did not address unique stressors, social context, and cultural values that may influence alcohol-related outcomes among Hispanics [21, 22]. Subsequently, we found that Hispanic patients receiving BMI from a Hispanic provider, and patients with lower levels of acculturation were more likely to benefit from BMI compared to those who received BMI from a non-Hispanic provider or were more acculturated [21]. Patient—provider ethnic concordance may have impacted the effectiveness of the intervention, for example, by implicitly adhering to culturally appropriate modes of communication. Further, less acculturated patients may have been more responsive to such modes of communication [21, 23].

### Necessity of cultural adaptations to brief motivational intervention

The need to culturally adapt behavioral interventions has been extensively acknowledged and justified [24–26], particularly if an evidence-based intervention is insufficiently successful in changing clinical outcomes for a particular ethnic group [27]. There is widespread agreement that more effective alcohol interventions could be developed for Hispanics by taking into account cultural values (e.g., familism) and acculturation experiences (e.g., acculturative stress) specific to Hispanics [28–30]. The necessity for comparing a culturally adapted brief motivational intervention (CA-BMI) to a non-adapted intervention among heavy drinking Hispanics is consistent with the recommendation by Miller and colleagues that such research constitutes an advance in the development of optimal approaches for treating understudied groups (e.g., Mexican-Americans) [31]. Despite the need for culturally adapted alcohol interventions among Hispanics [9, 15, 32], no comparative effectiveness study has empirically evaluated a culturally adapted BMI (CA-BMI) against a non-adapted BMI (NA-BMI). As such, this paper describes the design and implementation of a CA-BMI targeting heavy-drinking men of Mexican origin. The CA-BMI will target risk and protective factors that are especially relevant to this population.

Among Hispanics, acculturative stress has been identified as an important risk factor for drinking [8, 33–37] whereas familism has been found to be an important protective factor for reducing alcohol use [38–41], and increasing help seeking and treatment utilization [42–44]. We hypothesize that a CA-BMI that directly and consistently addresses acculturative stress, familism, and other cultural factors deemed relevant through formative work with the priority population and stakeholders, as described below, will result in significant reductions in alcohol problems and increases in help-seeking and treatment utilization among Hispanics, in addition to the reductions in alcohol use already observed with the NA-BMI.

### Process for culturally adapting brief motivational intervention

#### Community advisory board

For this study we will adopt the integrative practice framework, which identifies a continuum of stakeholder engagement processes from initial solicitation of participation to maintenance [45]. The concept of *best processes* for forming, operating, and maintaining is based on Green’s recommendations [46]. Key stakeholders will include patients and their families, health care providers, behavioral health specialists, and community treatment providers. Special emphasis will be placed on engaging stakeholders with expertise in working with Hispanic persons with alcohol problems. Through the active engagement of the community advisory board (CAB) throughout the proposed project we anticipate greater influence of patients and key stakeholders on the design, implementation, and interpretation of the study. In particular, the engagement of a CAB comprised of key stakeholders is critical to the refinement of the cultural adaptation initially proposed by study investigators.

Thus far, the CAB has been instrumental in developing the individual interview guides (see below) by helping researchers prioritize the questions of interest and asking them most effectively. The CAB has also aided in the interpretation of findings from the results of the individual interviews. Further, they helped researchers develop a comprehensive community guide to treatment options which informed making referral to treatment when appropriate. This reference materials reflect a broad range of services which may be of benefit to Hispanic males who were recently injured and engage in at risk drinking. In addition to medical detoxification, inpatient and outpatient services and alcoholics anonymous, these referrals included general counseling, physical and occupational rehabilitation, employment commission and other social services. The CAB has also provided feedback on the intervention itself including ways in which to be more culturally sensitive and responsive in addition to the adaptation itself. This was achieved, in part, by the development of videos reflecting the NA-BMI and potential components of the CA-BMI. In addition, the CAB has provided feedback on the selection of patient materials including psychoeducational information regarding heavy drinking and behavior change.

As part of study preparation and intervention adaptation, we will employ procedures consistent with recent models for intervention adaptation [29, 47], as was recently done by Castro and colleagues to adapt an evidence-based and theoretically driven motivational intervention for multiple cancer-risk behaviors among Hispanic smokers [48]. They used expert consultation, focus groups with the priority population, pretesting of program materials, and pilot testing of the intervention to culturally adapt an intervention being evaluated in a randomized controlled trial [48, 49].

#### Individual interviews and pretesting of materials

To further inform the CA-BMI, individual interviews will be conducted with at least 25 Mexican or Mexican American men recently admitted for an injury where they were drinking prior to the injury or engage in heavy drinking. Interviews will be facilitated in English and Spanish and sessions will last approximately 1 ½ hours. Trained interviewers will use a structured open-ended interview guide developed by the investigators, other study staff trained in qualitative methods, and CAB members. Questions are intended to inform adaptations by exploring issues around alcohol use, and treatment-seeking that are important to the priority population, and may need to be addressed in the CA-BMI. All interviews will be recorded and transcribed; transcripts will be coded by two individuals to capture salient themes using content analysis [50]. Interviews will also be used for pretesting of all potential study materials. Participants will provide feedback on the acceptability, appeal, preference, and usefulness of materials.

#### Pilot testing

After incorporating changes as a result of the individual interviews, CAB feedback and stakeholder feedback, the intervention protocol will be tested with 10 participants. Based on the pilot testing, counselors and patients will provide additional feedback on the intervention protocol. During piloting testing, the BMI and instruments will be tailored to better fit patients’ responses during pilot assessment, and BMI sessions.

### Accounting for patient and provider perspectives

The proposed study will measure a number of patient-centered outcomes. Alcohol use and alcohol problems have a significant impact on patients, their family and social networks, the community, and healthcare system. While these outcomes are of interest to patients and evaluators alike, treatment utilization and help-seeking are particularly important patient outcomes of interest. Based on feedback from patients, healthcare providers, behavioral health specialists, and community providers, we are broadening our definition of treatment utilization to include help-seeking from informal or cultural agents of behavior change that are likely to be accessed by Hispanics (e.g., church leaders, folk healers) [51].

The proposed study will also assess the feasibility and acceptability of the intervention from the perspectives of the patients and healthcare providers. Both NA-BMI and CA-BMI are based on MI principles and, therefore, explore patient preferences, and perspectives to develop a plan for change. As a result, we recognize the influence that the patient’s perspective of the intervention may have on targeted outcomes and will incorporate a measurement of patient satisfaction. We will be able to explore whether high ratings of satisfaction predict better outcomes from BMI. We will also be able to explore whether CA-BMI leads to greater patient satisfaction. The influence of patient satisfaction with BMI sessions on patient outcomes or a comparison across intervention strategies has not been routinely reported, as we propose here.

Ultimately, the dissemination and implementation of culturally adapted brief interventions in trauma care and emergency department settings rely upon organizational factors-most importantly, the perspective of healthcare providers. As a result, we will also assess the perceptions of CA-BMI and NA-BMI among healthcare providers as key stakeholders. First, the acceptability and feasibility of both interventions will be assessed prior and after patient recruitment. Evaluations of provider perspectives on the applicability, relevance, and potential adoption of a CA-BMI will be conducted. In this way, we can explore the impact of implementation of the protocol on provider perspectives and take into account the potential barriers and facilitators of dissemination and implementation. Second, like patient satisfaction, provider ratings of BMI will be assessed following CA-BMI and NA-BMI.

## Methods/Design

### Participants

#### Study site and recruitment

At present, approval has been obtained from the Institutional Review Boards from both The University of Texas at El Paso and University Medical Center (UMC) of El Paso. All data collection will be conducted at UMC of El Paso in El Paso, Texas. The ethical guidelines for research with human subjects followed by the present study protocol are compliant with the Helsinki Declaration. UMC is the largest public hospital (not-for-profit) located on the U.S./México border. It is a 396-bed, licensed, acute care facility and the only teaching hospital in the West Texas/Southern New Mexico region. UMC is also the only Level I Trauma Center within a 280 mile radius of El Paso. Eighty five percent of all trauma cases in the region annually are transported to UMC. In 2014, approximately 2,750 trauma patients were admitted to the UMC Trauma Center and approximately 75 % were Hispanic. The Emergency Department at UMC is also one of the busiest in the region, treating more than 55,000 patients annually, of whom approximately 80 % are Hispanic.

### Design and procedure

In this comparative effectiveness study, we will recruit 600 English- or Spanish-speaking heavy-drinking men of Mexican origin who are admitted to the hospital for medical treatment of an alcohol-related injury or heavy drinking. Participants will be randomized to receive a CA-BMI or NA-BMI. The primary outcomes of interest are alcohol use, alcohol problems, help-seeking, and treatment utilization. Follow-up assessments will be completed at 3, 6, and 12 months post-treatment. See Fig. 1.

**Fig. 1 Fig1:**
[figure not shown]
CONSORT diagram of participant flow

#### Screening

The UMC Clinical Coordinator and Screening Coordinator, in collaboration with other study staff, will ensure that comprehensive and standardized screening procedures are used to identify potentially eligible patients. At UMC, patients screen positive for an alcohol-related injury or heavy drinking based on 1) positive blood alcohol concentration (BAC), 2) initiation of a medical protocol for alcohol detoxification, or 3) a score ≥ 4 on the first three items of the Alcohol Use Disorders Identification Test (AUDIT-C), which is a gender-specific cut-off for heavy drinking among men. Based on current medical standards, all injured patients who have blood drawn have their BAC tested as part of routine laboratory tests. Once medically stable, all injured patients are screened by the UMC Screening Coordinator using the AUDIT-C, a standardized, internationally validated self-report measure of alcohol use, and heavy drinking [52, 53].

#### Inclusion/exclusion criteria

Eligibility criteria for this study are the following: 1) aged 18 or older, 2) treated for injury associated with a motor vehicle collision (involving driver, passenger, or pedestrian), a violence-related injury (i.e., gunshot, stab wounds, other assault related injuries), or a fall based on e-codes from the 10^th^ edition of the International Classification of Diseases, and 3) screen positive for an alcohol-related injury or heavy drinking as described above. Exclusion criteria are: 1) traumatic brain injury as indicated by a Glasgow Coma Scale score < 15 [54], or 2) cognitive impairment as indicated by a score of ≤ 24 on the Mini-Mental Status Exam (MMSE) [55, 56]. Patients who do not successfully complete the MMSE will be monitored regularly by the Screening Coordinator to reassess participation. Intoxicated patients at admission will be approached during their hospital stay once medically stable.

#### Ethnic identification

Ethnicity will be confirmed by study staff using procedures similar to general population surveys (i.e., 2010 census). Response options include: 1) no, not of Hispanic, Latino, or Spanish origin, 2) Yes, Mexican, Mexican American, Chicano, 3) Yes, Puerto Rican, 4) Yes, Cuban, or 5) Yes, another Hispanic, Latino or Spanish origin [57]. Patients who identify themselves of Hispanic, Latino, or Spanish origins, and only describe themselves as Mexican, Mexican American, or Chicano will be eligible to participate. In our prior study, 82 % of Hispanics identified themselves as Mexican, Mexican American, or Chicano only [20].

#### Randomization procedures

After obtaining informed consent, patients will complete the baseline assessment (described below). Subsequently, participants will be randomized to the CA-BMI or NA-BMI. Study staff will be blind to treatment assignment during the baseline assessment, and staff responsible for the assessment will not provide the intervention (vice versa). We will use an adaptive randomization procedure that minimizes imbalances in covariates [58] using a SAS macro [59]. This procedure ensures adequate distribution of key characteristics (i.e., acculturation, nativity, language of assessment) which have been found to influence outcomes [21].

### Brief motivational interventions

Both interventions (NA-BMI and CA-BMI) will adhere to MI principles [16, 17, 60], and practice of BMI. To help maintain the integrity of the two interventions, clinicians will be trained and supervised in the provision of only one of the interventions (NA-BMI or CA-BMI). As part of standard BMI protocols, all participants will receive personalized feedback based on results from their screening, as well as a personal drinking profile based on the results of the baseline assessment [61, 62].

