### Training and treatment fidelity

#### Interventionists

We have determined that Hispanics respond more positively to BMI, and that patient—provider ethnic matching significantly influences drinking outcome above and beyond the effect of the intervention. Both NA-BMI and CA-BMI will be provided by bilingual, bicultural, and same gender interventionists. Therefore, gender, ethnicity, and ability to speak both Spanish, and English will be held constant across interventions. By holding these three factors constant we can determine the differential influence of the two interventions on alcohol-related outcomes. To avoid contamination, providers of CA-BMI and NA BMI will be trained, and supervised separately throughout the study period. Study staff who are responsible for the intervention will not be responsible for baseline or follow-up assessments.

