### Approach to analyses

Analyses investigating group differences in alcohol problems, and treatment utilization will use random coefficient models [85, 86]. Longitudinal models will use the following sequence of steps recommended by Singer and Willett [86]: 1) examine empirical growth plots, 2) fit an unconditional means model, 3) fit an unconditional linear growth model, 4) fit an unconditional non-linear model, 5) determine the best model of longitudinal change by comparing models in the previous two steps using the Akaike information criterion (AIC), 6) select the most appropriate error covariance structure using AIC, and 7) add level-2 predictors (e.g., intervention group).

Potential moderators will be examined by constructing interaction terms between treatment, and a priori moderator variables (e.g., acculturative stress and familism) to examine the possibility that the relation between a putative moderator, and outcome differ across treatments [87]. Mediation analysis (per recommendations by MacKinnon [2008]) will be conducted using a growth-curve framework implemented in an SEM [88]. Models will be constructed by first fitting growth models for mediators, and outcomes, and then fitting mediational growth models. Latent growth models will be comprised of at least two latent factors; one factor will represent the initial status, and one or more factors will represent the growth rate of a variable. The growth factor of the mediator will be regressed on the initial status of the mediator, the outcome, and the intervention group. A significant intervention effect establishes a relation between the intervention group, and the mediator, controlling for baseline levels of the mediator and outcome. Next, the growth factor will be regressed on the initial status of the mediator, the outcome, the slope of the mediator, and the intervention group. A significant effect of the mediator growth factor establishes a relation between change in the mediator, and change in the outcome, controlling for baseline levels of mediators and outcome.

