Power estimates were derived as the proportion of significant effects (two-tailed α = .05) across like simulations [94]. We simulated 10,000 data sets of 400 observations under the assumption that missing data will be ameliorated with the strategies described in the missing data section, and all participants will contribute data to the analysis. Intraclass correlation was simulated at .65 based on the intraclass correlations observed in our prior study. Power was .81 for continuous outcomes, and .83 for binary outcomes. A power analysis for a moderation effect by simulating a three-way interaction between treatment, time, and a moderator (e.g., familism) was conducted. Per Kraemer and colleagues’ recommendations, the interaction was examined using plots, confidence intervals, and *p* values [95]. We investigated the power for a hypothesized contrast at high, and low levels of a moderator (e.g., low v. high acculturative stress in participants in CA-BMI) through a simple slope contrast at 1 SD ± the moderator mean for participants [96]. Power for an effect size equivalent to *d* = .29 was .78 for a continuous outcome, and power for an effect size equivalent to *h* = .27 was .82 for a binary outcome. Power analysis for the proposed mediation model was conducted using a Monte Carlo simulation [90]. Using standardized regression coefficients, we conducted a simulation for 10,000 data sets in which the path from the intervention to the mediator was .12 (equivalent to *d* = .22), and the path from the mediator to the outcome was .30 for standardized variables, reflecting the stronger relation that we anticipate between the mediators and outcomes. The Monte Carlo simulation indicated that power for the indirect effect was .77. Thus, accounting for a potential 20 % participant attrition, the proposed sample size should provide sufficient power for all planned analyses.

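### Each interventionist delivers only one arm, but neither the outcome model nor the power simulation has an interventionist level; if outcomes vary between clinicians, the arm contrast is too precise and the stated power too high.

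*Protocol article*

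**What the plan says.** **Delivery.** Under Brief motivational interventions, "clinicians will be trained and supervised in the provision of only one of the interventions (NA-BMI or CA-BMI". Under Interventionists, "providers of CA-BMI and NA BMI will be trained, and supervised separately throughout the study period". No clinician works in both arms.

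**Claim drawn from the design.** Interventionists says that "gender, ethnicity, and ability to speak both Spanish, and English will be held constant across interventions", and concludes: "By holding these three factors constant we can determine the differential influence of the two interventions on alcohol-related outcomes". The same paragraph reports that "patient—provider ethnic matching significantly influences drinking outcome above and beyond the effect of the intervention".

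**Model.** Approach to analyses states: "Analyses investigating group differences in alcohol problems, and treatment utilization will use random coefficient models". After choosing the growth form and the error covariance by AIC, the last step is to "add level-2 predictors (e.g., intervention group". The moderation and mediation descriptions that follow add no interventionist term either.

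**Power.** Power analysis reports a completed Monte Carlo study: d = .28 (continuous) and h = .28 (binary), two-sided alpha .05, data sets of 400, power .81 and .83. On correlation it says only: "Intraclass correlation was simulated at .65 based on the intraclass correlations observed in our prior study". No number of interventionists, caseload or interventionist ICC is given.

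**The concern.** With clinicians nested in arm, the difference between the arm means contains the difference between the average clinician effects of the two teams. A model with occasions within participants treats one clinician's patients as independent given arm, so that component is missing from the error term. Matching on gender, ethnicity and language leaves individual differences in skill or rapport untouched.

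The central comparison of the trial is at stake. Intervals would be too narrow, a nominal 5% test would reject too often, and a difference between the two sets of clinicians could be reported as an effect of cultural adaptation.

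**Working it through.** **Inputs from the article.** d = .28; two-sided alpha .05; 400 simulated, read as 200 participants per arm; 600 recruited at about 1:1; 20% attrition, leaving 600 × .80 = 480.

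**Assumed, because the article is silent.** k interventionists per arm, 4 or 10; interventionist ICC ρ of 0 to .05; equal caseloads.

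**Step 1: reproduce the stated power.** With independent participants, SE = √(2/200) = .10 and .28/.10 = 2.80. Power = Φ(2.80 − 1.96) = Φ(.84) = .80, against the stated .81. For h = .28 the same approach gives .79 to .80 for control rates of .10 to .50, against .83. The binary simulation settings are not given, so that gap is not called an error. The continuous figure agrees with a calculation that has no interventionist variance.

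**Step 2: which ICC is the .65?** It is stated for the longitudinal mixed-model simulation. It cannot be an interventionist ICC. Even with 10 per arm (20 patients each), the design effect would be 1 + 19 × .65 = 13.35, so 2.80/√13.35 = .77 and power = Φ(.77 − 1.96), about .12.

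**Step 3: add interventionist variance.**
- Caseload m = N/(2k); design effect DEFF = 1 + (m − 1)ρ.
- The true SE exceeds the model's SE by the factor √DEFF.
- Type I error of the unadjusted test = 2[1 − Φ(1.96/√DEFF)].
- Power of a valid test has noncentrality .28/√(2·DEFF/(N/2)). It is given on the normal approximation and on t with 2(k − 1) df.

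Example, N = 400, k = 4, ρ = .02: m = 50; DEFF = 1 + 49 × .02 = 1.98; √DEFF = 1.41; 1.96/1.41 gives type I error .164; noncentrality 2.80/1.41 = 1.99; power .51 (normal), .39 (t, 6 df).

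| k per arm | ρ | DEFF | SE factor | Type I error, unadjusted | Power, normal | Power, t |
|---|---|---|---|---|---|---|
| 4 | 0 | 1.00 | 1.00 | .050 | .800 | .648 |
| 4 | .01 | 1.49 | 1.22 | .108 | .631 | .486 |
| 4 | .02 | 1.98 | 1.41 | .164 | .512 | .388 |
| 4 | .05 | 3.45 | 1.86 | .291 | .325 | .247 |
| 10 | 0 | 1.00 | 1.00 | .050 | .800 | .754 |
| 10 | .01 | 1.19 | 1.09 | .072 | .728 | .680 |
| 10 | .02 | 1.38 | 1.17 | .095 | .664 | .616 |
| 10 | .05 | 1.95 | 1.40 | .160 | .518 | .475 |

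Part of the fall in the last column comes from the few degrees of freedom alone, as the ρ = 0 rows show.

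**Step 4: does the margin over 400 absorb it?** With 480 completers and ρ = 0, power is .87 (normal). The margin is a factor of 480/400 = 1.2, so it is used up when DEFF reaches 1.2. That is ρ = .2/59 = .0034 with 4 per arm (m = 60), or .2/23 = .0087 with 10 per arm (m = 24). At 480, k = 4 and ρ = .01/.02/.05, type I error is .12/.18/.32 and power on 6 df .53/.42/.26. With 10 per arm, type I error is .08/.11/.18 and power .74/.67/.51.

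**Step 5: which random effect is needed?** Randomization procedures places the baseline assessment before randomization, so a clinician can affect only what follows. Write the interventionist term as u_j, added equally at baseline and follow-up. In the change from baseline it is u_j − u_j = 0. A plain random intercept therefore largely drops out of the group-by-time contrast and leaves its standard error uncorrected. The term must act on change after baseline.

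**The case against.** **The interventionist ICC could be zero.** The article gives no ICC, team size or caseload, and the results above run from mild to severe. This stands. A reader might infer that the standard errors are certain to be too small, or that two small teams are planned. The article supports neither. The direction of the error is conditional on clinician variance, and its size is unknown.

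**Clinician differences are controlled.** The training and fidelity sections provide a two-day training, weekly supervision, on-site observation at least monthly, six-monthly boosters, adherence checklists and an expert-level MITI threshold. The session lasts about 25 minutes. These measures bear on whether an ICC as high as .05 is plausible, but they do not show that it is zero.

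**The article's own evidence of provider effects concerns ethnic matching.** This also stands. A reader might take that finding as proof of variation among these clinicians, but ethnicity is one of the three features held constant in both arms. It shows that providers can matter, not that matched clinicians differ.

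**This is detail for the full plan.** Partly fair: the model steps are generic, do not exclude a further level, and degrees of freedom are commonly left to an analysis plan. But the article fixes where arm enters the model, reports a finished simulation with one ICC, and claims that three matched features suffice to determine the effect of the interventions. Those are stated choices that sit badly with the stated delivery design.

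**The arithmetic is simplified.** It uses a single contrast and equal caseloads. In a growth model the relevant ICC is that of the slope or follow-up contrast. This affects the size, not the direction.

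**Conclusion.** The point holds in conditional form. Interventionists are nested in arm, and neither the stated model nor the stated simulation carries interventionist variance. Whenever that variance exceeds zero, the plan as written understates the standard error of the arm contrast, exceeds its nominal type I error and overstates power.

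For the assumed 4 to 10 interventionists per arm and ICC .01 to .05 at N = 400, the standard error is understated by a factor of about 1.1 to 1.9. These figures are illustrations, not estimates for this trial. The omission itself can be stated with confidence; its magnitude cannot.

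**What to change.** 1. Record the interventionist for each session; the article does not say that this is done.
2. In every between-arm outcome model, add an interventionist random effect nested in arm that acts on change after baseline: a random slope on time, or a random effect on post-baseline visits only. An intercept shared by baseline and follow-up is not enough. Use Kenward-Roger or Satterthwaite degrees of freedom where available.
3. Rerun the power simulation for the planned number of interventionists per arm over an ICC range such as 0 to .05, and report the result beside .81/.83. Enrolment need not change.
4. Reword the conclusion under Interventionists so that matching on gender, ethnicity and language is not said by itself to isolate the intervention effect.

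The cost is one recorded variable, one more variance component and a repeated simulation. The price in results is wider intervals and a less favourable stated power.
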